##### Protocol Development

In conjunction with our risk prediction model, the findings from our aim 1 stakeholder interviews will directly inform our protocol for identifying persons who are at increased risk for HIV and likely to benefit from PrEP. This will include elements, such as which practitioners receive EHR alerts about potential PrEP candidates and the content of staff trainings for collecting and acting on patient-reported data and EHR alerts. We will select a final process for identifying candidates for PrEP discussions based on sensitivity (ie, missing as few persons at increased risk as possible), feasibility, and efficiency, while taking into account priorities identified by stakeholders in aim 1.

A key consideration for sexual health discussions in the jail setting is privacy. Feedback in aim 1 will inform how and where these discussions will take place. Providers may also desire additional training in assessing sexual risk, as knowledge of PrEP among correctional nursing staff and clinical providers is vital for successful implementation [78]. Furthermore, the approach to incarcerated individuals about sensitive topics, such as sexual health and substance use, will be informed by best practices, including having these screenings conducted one-on-one by medical staff and partnering with community-based organizations [79]. Any paper materials given to patients will be adapted to the American Medical Association’s recommended 6th grade reading level and worded to avoid disclosing the health status.

##### Navigation for Individuals Likely to Benefit From PrEP

Individuals who are identified as being at increased risk for HIV and who test negative for HIV will be considered PrEP candidates. We will develop a PrEP decision-support tool to be used with the diverse populations present in the jail, informed by stakeholders’ preferences from aim 1. This will include presenting information on sexual health and HIV prevention for multiple populations (eg, transgender people and cisgender women), local details on HIV epidemiology, and ways to afford and access PrEP. Individuals identified as PrEP candidates will meet with medical providers or navigators (depending on stakeholders’ preferences) to review HIV prevention options and our patient decision-support tool. Patients will be informed that they will not be charged for these visits, as for all care related to communicable diseases in the DCJ. At this visit, the provider or navigator will assess the patient’s knowledge of and interest in PrEP. Together with the patient, they will work through the decision-support tool. If the patient plans to pursue PrEP care after incarceration, the navigator will initiate the navigation protocol.

##### PrEP Care Navigation and Linkage Following Release

Those interested in PrEP will receive intensive navigation that includes both in-person and electronic referrals. Similar to existing navigation protocols (eg, for hepatitis C [80]), the navigator will initiate this process while the individual is still in jail. The navigator will obtain detailed patient contact information, identify and address the patient’s health priorities and potential barriers to care, and create a personalized step-by-step process for accessing PrEP services after release. Patients will also be able to contact the navigator after jail release directly by phone or SMS text messaging.

Multiple PrEP providers in the Dallas community employ peer outreach workers who accompany patients to their PrEP visits. We will work with these providers to develop a protocol for seamless hand-off from the jail-based navigator to the community-based peer. For electronic referrals, we will integrate stakeholders’ preferences for details regarding the transfer of information to community PrEP sites, including what information to communicate, how to communicate, and the timing of communication. Findings from our aim 1 qualitative data will help us pinpoint solutions to barriers or competing priorities to PrEP that patients identify. In some cases, we anticipate that multiple referrals will be necessary for patients to successfully access PrEP.

#### Aim 3: Implementation and Sustainment

In aim 3, we will deploy our multicomponent strategy at the DCJ and assess its impact on implementation and clinical outcomes for PrEP, as specified in Table 1.

**Table 1 table1:** Quantitative implementation outcomes, metrics, timing, and data source.

Hybrid type 3 domain and outcome		Metrics (among patients with high risk)	Timing (month range)	Data source^a^
**Implementation**				
	Feasibility	HIV/STI^b^ testing offered	1-24	EHR^c^, navigator
	Feasibility	PrEP^d^ discussions offered	1-24	EHR, navigator
	Feasibility	Shared decision-making tool offered	1-24	EHR, navigator
	Feasibility	PrEP navigation visits offered	1-24	EHR, navigator
	Feasibility	PrEP referrals offered	1-24	Navigator
	Penetration	Providers discuss/refer for PrEP	1-24	EHR, navigator
	Acceptability	HIV/STI testing completed	1-24	EHR
	Acceptability	PrEP discussions completed	1-24	EHR, navigator
	Acceptability	Shared decision-making tool used	1-24	EHR, navigator
	Acceptability	PrEP navigation visits completed	1-24	EHR, navigator
	Acceptability	PrEP referral completed	1-24	Navigator
**Effectiveness**				
	PrEP	PrEP visits in the community	1-24	Navigator
	PrEP	PrEP prescription	1-24	Navigator
	PrEP	PrEP use at 3 months	1-24	Navigator
	HIV/STI	New HIV/STI diagnoses	1-24	EHR
**Sustainment**				
	All	Reassess all study outcomes	25-30	All

^a^Qualitative assessments (3 times per year) complement quantitative metrics for all outcomes.

^b^STI: sexually transmitted infection.

^c^EHR: electronic health record.

^d^PrEP: pre-exposure prophylaxis.

##### Training of DCJ Staff

The project principal investigators will conduct a 2-session interactive group training for frontline DCJ practitioners to introduce our PrEP implementation strategy. Session 1 will be adapted from trainings on culturally competent sexual health care, HIV, and PrEP [81], including clinical indications for PrEP and barriers and facilitators to its adoption in the jail and local community. Session 2 will introduce the rationale and practical aspects of using patient-reported and EHR data to identify PrEP candidates, as our prior qualitative work suggests that providers are more likely to trust, adopt, and use HIV risk assessment tools if they understand how they work [82]. The session will also review how providers and navigators can engage patients in the shared decision-making process and will include demos of PrEP decision-support tools. Lastly, session 2 will cover PrEP navigation processes, including PrEP resources in Dallas County, and navigation protocols. Postsession evaluations will be conducted for rating quality and usefulness.

##### Steps for Strategy Implementation

Our strategy will include the following detailed steps that can be visualized as part of the continuum (Figure 2): (1) identify, (2) engage, and (3) navigate.

**Figure 2 figure2:**
[figure not shown]
Intervention steps in the jail-to-community continuum. DCJ: Dallas County Jail; EHR: electronic health record; PrEP: pre-exposure prophylaxis; STI: sexually transmitted infection.

In the “identify” step, when individuals enter the jail, a jail EHR record will be created (or an existing record will be opened for those with prior DCJ incarceration). Our automated algorithm will match the jail EHR to the Parkland EHR and generate an individual HIV risk score. For people with predicted HIV risk above a prespecified threshold that maximizes sensitivity without causing alert fatigue among providers, an automated prompt will appear in the jail EHR for providers to discuss PrEP and order HIV/STI testing. As illustrated in Figure 2, providers will also be prompted to order HIV/STI tests for any patients who report risk factors at intake or during a clinical assessment (eg, transgender identity and requests to be housed with MSM) or who request testing directly. Prompts will persist until orders are completed as a “nudge,” a behavioral economic intervention to maximize ordering [83], and results are entered into the EHR.

In the “engage” step, positive HIV tests will prompt referrals to the jail HIV clinic for rapid initiation of antiretroviral therapy according to the current practice, and STIs will be treated based on CDC guidelines [84]. Persons with negative HIV tests will meet one-on-one with a provider or PrEP navigator and receive counseling informed by our PrEP decision-support tool. The navigator we hire will be experienced in working with CL-involved people. Counseling will be person-centered and culturally tailored, with positive sexual health framing.

In the “navigate” step, for patients interested in PrEP, the navigator will review a list of PrEP clinic locations and assist with selecting a provider. Once an individual is released from the DCJ, the navigator will facilitate PrEP linkage by contacting that individual (by phone or SMS text messaging) and providing personalized care navigation. A hotline will be available for released individuals to call for assistance with PrEP referrals. The navigator will continue to follow referred patients for 3 months after any PrEP initiations, recording these contacts and clinical outcomes in REDCap, a secure online data capture system [85].

For this aim of the study, the patient navigator will obtain verbal consent from patients to proceed with a discussion on sexual health and to contact them after release from jail. The navigator will use a script to inform patients about the goals of the project, including the metrics to be collected, and reinforce that the meeting with the navigator is voluntary and will not affect the legal status of the patients.

We will track quantitative and qualitative metrics related to our implementation strategy during a 24-month period of iterative assessment and refinement. Our study metrics map directly to the EPIS framework at key steps in the PrEP care continuum (Figure 2). As shown in Table 1, we will assess quantitative effects, including the number of patients who attend a community PrEP visit, initiate PrEP, and persist with PrEP use for ≥3 months, which is a robust HIV prevention outcome [7]. We will track the rates of new and previously known HIV diagnoses and STIs in the DCJ through EHR chart review.

##### Feasibility

Feasibility refers to the extent to which a practice change can be successfully used or carried out within a specific setting [86]. We define feasibility as >65% of eligible patients being offered HIV/STI testing and one or more PrEP discussions, our patient PrEP decision-support tool, a PrEP navigation visit, or a PrEP referral in jail.

##### Penetration

Penetration refers to the extent to which a practice is integrated within a specific setting [86]. For this metric, we will track the proportion of providers who discuss PrEP or refer to a navigator for at least one eligible patient.

##### Acceptability

Acceptability refers to the perception among setting stakeholders that a practice is agreeable, palatable, or satisfactory [86]. We will calculate the proportions of patients who accept offers for one or more HIV testing, STI testing, PrEP discussion, navigator contact, or PrEP referral, with acceptance of >80% of test offers and >65% of discussion offers considered acceptable based on prior studies [35,87-89]. We will evaluate differences in feasibility and acceptability among patients by age, sex, gender identity, and race or ethnicity to identify imbalances in the offering and uptake of testing and referrals.

##### Effectiveness Regarding PrEP Outcomes

Additionally, on a monthly basis, we will measure the proportion of individuals who test negative for HIV, the proportion of this subgroup who receive notifications of their HIV test results, and the proportion of all those tested who are candidates for PrEP based on US Public Health Service practice guidelines for PrEP [90].

Among these PrEP candidates, we will assess how many are released to the community and how many are successfully contacted by the jail navigator after release. We will track the proportion of candidates attending ≥1 PrEP visit after jail release, the proportion prescribed PrEP, and the proportion using PrEP at 3 months after initiation (using direct patient assessments by the navigator). We will complete a run chart, which we will adapt from quality improvement methodologies [91], to evaluate trends in the PrEP care cascade [92] on a monthly basis during the 24-month intervention period and the additional 6-month sustainment period.

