##### Datasets to Identify Individuals at Increased Risk for HIV

The Parkland Center for Clinical Innovation (PCCI) has developed and validated an automated matching algorithm to extract data from the DCJ EHR (PEARL) and match it to data from Parkland’s EHR (Epic) from 2010 to the present. Records will be matched based on multiple variables, including patient name, preferred name, date of birth, gender, sex assigned at birth, race or ethnicity, and social security number as available. We will exclude any individuals younger than 18 years. Individuals may have multiple encounters in both the jail and Parkland EHRs due to repeat jail incarcerations or medical visits, and these data will be incorporated as summary variables (eg, number of prior episodes of gonorrhea) with statistical adjustments for repeated measures in an individual. This combined dataset will provide rich data for identifying PrEP candidates and allow us to develop an HIV prediction model. This component of the study will involve the collection of existing data and the development of tools and protocols, and therefore, a waiver of consent will be obtained. Furthermore, matching of records using the identifiers above will be performed behind the firewall of the PCCI, and all datasets will be deidentified prior to sharing with the rest of the research team.

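### Table 1 names the navigator, who also delivers post-release linkage, as the only quantitative source for all three PrEP outcomes, although matched Parkland records could serve as a partial second source

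*Protocol article*

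**What the plan says.** The Effectiveness block of Table 1 reads "PrEP visits in the community 1-24 Navigator", "PrEP prescription 1-24 Navigator" and "PrEP use at 3 months 1-24 Navigator". The fourth row of that block has a different source: "New HIV/STI diagnoses 1-24 EHR". Of the 11 implementation rows above it, eight list both the EHR and the navigator, one lists the EHR alone and two (referrals offered, referrals completed) list the navigator alone. A footnote says that qualitative assessments three times a year complement all outcomes.

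Under Steps for Strategy Implementation, the navigator contacts released people by phone or SMS, provides the navigation, follows referred patients for 3 months after PrEP initiation, and enters contacts and clinical outcomes in REDCap.

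Effectiveness Regarding PrEP Outcomes takes proportions of PrEP candidates for visits, prescription and 3-month use. The parenthesis "using direct patient assessments by the navigator" follows 3-month use. The section also counts "how many are successfully contacted by the jail navigator after release" as a separate step.

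Under Sustainment, baseline linkage is put at essentially zero, so linkage is reported as a proportion with 95% CIs and no pre/post comparison. Retention up to 6 months again relies on navigator follow-up.

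On records, the section on datasets says the clinical innovation centre has "developed and validated an automated matching algorithm to extract data from the DCJ EHR" and match them to Parkland's EHR. Ethical Considerations lists encounters and prescriptions among the jail and Parkland data.

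**The concern.** The person who delivers the linkage service is the only named recorder of whether it worked. Two errors are possible, in opposite directions. A candidate who attends a clinic but is never reached may be recorded the same way as one who never attended. And a navigator who has worked to link a patient may accept a report of linkage that a record would not bear out.

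In a comparative analysis part of such error might cancel. Here the estimate is a single uncontrolled proportion, so any error passes straight into it. The 95% CI describes sampling variation only. The monthly run chart of the PrEP cascade is exposed too: a change in contact success could look like a change in linkage.

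**Working it through.** No figure in the plan depends on this point. There is no target, sample size or power for linkage, and no expected contact rate, so there is nothing to reproduce. The size can only be illustrated, and every input below is an assumption.

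**Notation.** c = share of candidates reached after release; p_r = linkage among those reached; p_u = linkage among those not reached; s = share of the unreached patients' PrEP visits that take place at Parkland. The illustration assumes that the navigator learns correctly of every linkage among reached patients and of none among the others.

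- True linkage = c·p_r + (1 − c)·p_u
- Navigator-only linkage over all candidates = c·p_r
- Either source (navigator or Parkland EHR) = c·p_r + (1 − c)·p_u·s

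**With p_r = 30% and p_u = 15%:**

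| c | True | Navigator only | Either, s = 10% | Either, s = 30% | Either, s = 50% |
|---|---|---|---|---|---|
| 30% | 0.09 + 0.105 = 19.5% | 9.0% | 10.05% | 12.15% | 14.25% |
| 50% | 0.15 + 0.075 = 22.5% | 15.0% | 15.75% | 17.25% | 18.75% |
| 70% | 0.21 + 0.045 = 25.5% | 21.0% | 21.45% | 22.35% | 23.25% |

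The EHR narrows the gap and closes it only at s = 100%. The documents do not give Parkland's share of PrEP care.

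**Against the sampling error.** With an assumed 500 candidates, the 95% half-width at 15% is 1.96 × √(0.15 × 0.85 / 500) = 3.1 points. The gap at c = 50% is 22.5 − 15.0 = 7.5 points. If p_u were 10% instead, true linkage would be 0.15 + 0.5 × 0.10 = 20% and the gap 5 points. If p_u were zero there would be no gap.

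**Worst-case bounds.** If nothing is assumed about the unreached, linkage lies between c·p_r and c·p_r + (1 − c). With p_r = 40% and c = 50% that is 20% to 70%; at c = 90% it is 36% to 46%.

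**Why record confirmation should not be the headline.** With true linkage of 22.5%, 30% of all visits at Parkland and no confirmation from other clinics, record-confirmed linkage would be 0.30 × 22.5% = 6.75%. That is further from the truth than the navigator's 15%.

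**Over-reporting.** The either-source rule does not remove it, since a wrong navigator report still counts. Only the side-by-side comparison gives a view of it, and only for care that should appear at Parkland.

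**The case against.** The strongest reply is that naming the navigator as source does not mean patients' word alone. Patient assessment is tied only to 3-month use. The section on navigation and linkage following release plans electronic referrals and a hand-off to community peers, and notes that some providers' peers accompany patients to visits. A hotline and SMS supplement phone calls. The navigator may therefore learn of visits from clinics or peers, including for patients who never answer. This stands: a reader might infer that all three outcomes are self-reported and hinge on who picks up the phone, and the text does not support that. But clinic confirmation is not named as an outcome source.

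Second, the cascade already uses candidates as its denominator and reports contact separately. A reader might infer that unreached people drop out of the proportion; that section does not say so. Post-release contact is also part of the intervention, so low reach can mean truly low linkage. Both points stand. Neither identifies a linked but unreached candidate.

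Third, the article is condensed, and verification details usually sit in the full protocol or SAP. That covers how a visit is verified. The source itself, however, is fixed in Table 1.

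Fourth, the EHR is no ready replacement. The match reaches only Parkland, while several community providers offer PrEP. Results lists Parkland integration for the risk model as future work, and the aim 2 waiver covers identifying subjects and building the model. This stands and limits the fix to a partial cross-check. Steps for Strategy Implementation does, however, already plan the match at jail entry within aim 3.

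**Conclusion.** The point holds in a limited form. All three PrEP outcomes have one quantitative source, that source is the person delivering post-release linkage, and the headline is an uncontrolled proportion whose CI does not reflect ascertainment error. Candidates who link without being reached cannot be told reliably from those who do not link.

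The size is unknown. In the illustrations the shortfall runs from 4.5 points (70% reached) to 10.5 points (30% reached), resting on assumed linkage of 30% among those reached and 15% among the rest, and on the navigator having no other route to the unreached. A reader might infer that linkage will be overstated because the deliverer scores the result. The documents do not support a net direction, since missed events pull the other way.

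The improvement is worth making because a partly independent source is already planned for another purpose. It does not reach 3-month use, which stays with the navigator.

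**What to change.** - In Table 1, change the data source for the rows on PrEP visits and PrEP prescription from the navigator alone to the navigator plus EHR (matched Parkland records).
- Count a candidate as linked if either source shows a visit or a prescription.
- Keep the candidate denominator of Effectiveness Regarding PrEP Outcomes, restricted to candidates released to the community.
- Report record-confirmed and navigator-only linkage side by side, without making the record-confirmed figure the headline.
- Show linkage among those reached as a sensitivity analysis.

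**Cost.** A table edit and modest data work to query Parkland encounters and prescriptions for released candidates. Use of Parkland records as an outcome source must be covered in the aim 3 IRB submission and in the navigator's verbal consent script; the article lists approval only for aims 1 and 2, so there may still be room to add this. The submission should also say whether candidates who never meet the navigator, and so never hear the script, are covered.

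**Downside.** Visits at other community providers still depend on the navigator, so the check is partial and its yield depends on Parkland's unknown share of PrEP care.

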##### Effectiveness Regarding New HIV/STI Diagnoses

We will also track STIs and new and previously known HIV diagnoses in the jail among priority groups and the general jail population. STI positivity will be calculated as positive tests per the total number of tests completed. New HIV diagnosis rates will be calculated as confirmed positive test results in persons without a prior diagnosis of HIV per the total number of tests completed within a given time period. We will use an interrupted time series analysis using monthly data points to compare rates during the 24 months before and 24 months after our intervention is implemented. Our primary analysis will involve a comparison of the longitudinal rates before and after the intervention, and a mixed effects model for interrupted time series will be used as a secondary analysis. We will conduct linear regression analyses to determine if there is a significant difference in new HIV diagnosis rates before and after the intervention.

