##### Sustainment

Sustainability refers to the extent to which a new practice is maintained or institutionalized within a setting’s ongoing operations [86]. We will assess how well the strategy components are maintained as part of existing jail processes for 6 months after the formal 24-month study period, including tracking retention in PrEP care for up to 6 months (through navigator follow-up). Our research team includes dissemination consultants, who are medical providers working in jails in Austin, TX; Chicago, IL; and Boston, MA, and who will offer input on refining our strategy components for ongoing use at the DCJ and the potential transfer and integration into other jail settings.

For PrEP linkage, current rates of linkage are essentially zero. Thus, in lieu of a pre/post comparison, we will report the proportion of patients linked to PrEP care during the implementation period with 95% CIs. Power analysis is performed for the interrupted time series analysis of monthly HIV positivity rates, assessing the difference in the mean between the 24 months before and after implementation. Over the preimplementation period, an anticipated 250 tests will be performed monthly with 3 new HIV diagnoses per month. In the postimplementation period, of 500 HIV tests per month, an increase to 9 new diagnoses per month is anticipated due to the focus on individuals identified by the prediction model as being at increased HIV risk. Furthermore, we assume a correlation of 0.2 among monthly observations. Based on a mixed effects Poisson regression model, we can detect the difference in the mean HIV-positive rate between the 2 periods with >80% power at a 2-sided type I error of 0.05. We will also perform subgroup analyses, comparing testing rates by sex, age group, and race or ethnicity.

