## Results

The study was funded by the National Institute of Mental Health in April 2022. Progress has been made on various aims to date. Qualitative interviews have been completed with 26 individuals, including 9 formerly incarcerated individuals, 9 county jail staff, and 9 employees of community organizations (1 individual was both a formerly incarcerated individual and an employee of a community organization). A focus group with 10 additional individuals has also been conducted. All interviews have been transcribed, coded, and analyzed, and a manuscript highlighting the key themes is in progress.

In addition, summaries of field notes for each interview have been organized into key barriers; facilitators; suggested approaches to overcome barriers; resources needed to overcome barriers; and specific strategies to improve risk assessment, HIV testing, sexual health or PrEP education during incarceration, and postrelease linkage to PrEP. Findings from these interviews have been applied to formulate a jail PrEP implementation protocol using rapid qualitative analysis.

An HIV risk prediction model based on jail EHR data to identify individuals most likely to benefit from PrEP has been developed using records from 33,458 individuals who have undergone HIV testing in jail. This model has been optimized using machine learning, has been internally validated, and is ready to be deployed. Future exercises will include integration with health system EHR data from Parkland Hospital and comparisons to parsimonious models, which will guide the iterative development of the model. We anticipate that preliminary study findings on the implementation and effectiveness of the jail PrEP implementation strategy will be available in 2026. 

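### The new-HIV rate leaves people with known HIV out of the numerator but keeps their tests in the denominator, so a change in their share of tests moves the before/after ratio

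*Protocol article*

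**What the plan says.** Under Effectiveness Regarding New HIV/STI Diagnoses, the rate is "confirmed positive test results in persons without a prior diagnosis of HIV per the total number of tests completed within a given time period". The same section plans to "compare rates during the 24 months before and 24 months after our intervention is implemented", using monthly points. It also tracks previously known HIV diagnoses.

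The power calculation, under Sustainment, is for this comparison. Before implementation, "an anticipated 250 tests will be performed monthly with 3 new HIV diagnoses per month". Afterwards, "of 500 HIV tests per month, an increase to 9 new diagnoses per month is anticipated", and the rise is put down to the focus on people whom the prediction model flags as higher risk. Claimed power is above 80% at two-sided 0.05, with a correlation of 0.2 among months.

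On who is tested, Steps for Strategy Implementation prompts testing for anyone above the risk threshold, anyone reporting risk factors and anyone asking for a test. It states no exclusion for people already known to have HIV. A negative HIV test is required only later, for PrEP candidacy.

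On how new and known cases are told apart, the same section says: "We will track the rates of new and previously known HIV diagnoses and STIs in the DCJ through EHR chart review". It does not name the record or the look-back.

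**The concern.** Numerator and denominator describe different populations. The numerator is drawn from people who could still receive a first diagnosis; the denominator also holds tests in people who could not. The recorded rate is therefore the yield among people at risk, diluted by the known-HIV share of tests.

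A constant dilution cancels from the ratio. A changing one does not, and the strategy is designed to change who is tested. Part of a before/after difference could then reflect a different share of uninformative tests rather than better or worse case-finding. This matters because it is the only outcome for which the article calculates power, and its only stated before/after test on HIV diagnoses.

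**Working it through.** **Inputs from the article.** Before: 3 diagnoses in 250 tests a month for 24 months, so 72 in 6,000 (rate 0.012). After: 9 in 500 a month for 24 months, so 216 in 12,000 (rate 0.018). Ratio 0.018/0.012 = 1.50.

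**Assumed inputs.** k0 and k1, the known-HIV share of tests before and after. The article does not give them. Its only related figure is 1.4%, an HIV prevalence for Texas prisons in the Introduction; that is not a share of tests at this jail.

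**Reproducing the planned power.** Wald test on the log rate ratio, months independent:

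- SE = √(1/72 + 1/216) = 0.1361
- z = ln(1.50)/0.1361 = 0.4055/0.1361 = 2.980
- Power = Φ(2.980 − 1.960) = 84.6%

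This agrees with the claim of more than 80%. The structure of the 0.2 correlation is not stated; under a first-order autoregressive reading the same calculation gives 68.2%. The power figures below use independent months and serve only for comparison with 84.6%.

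**Effect of the denominator.** Let y be new diagnoses per test among people without a prior diagnosis. With known share k, the recorded rate is y(1 − k), so

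recorded ratio = (y1/y0) × (1 − k1)/(1 − k0).

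Take y1/y0 = 1.50, keep 72 events before, and let events after be 216 × (1 − k1)/(1 − k0):

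| k0 → k1 (assumed) | Recorded ratio | Power |
|---|---|---|
| equal | 1.50 | 84.6% |
| 1% → 3% | 1.50 × 0.97/0.99 = 1.47 | 80.6% |
| 1.4% → 5% | 1.50 × 0.95/0.986 = 1.45 | 76.8% |
| 5% → 0 | 1.50 × 1/0.95 = 1.58 | 92.2% |

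**If yield among people at risk does not change** (y1/y0 = 1), the recorded ratio is 0.97/0.99 = 0.980 for 1% → 3%, 1/0.986 = 1.014 for 1.4% → 0, and 1/0.95 = 1.053 for 5% → 0. In the last two cases the nominal 5% test rejects about 5.1% and 6.5% of the time.

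**The case against.** The strongest reply is that the effect is small and may be nil. It vanishes if the known-HIV share is constant, and it is nil if people with known HIV are hardly ever tested. The model is trained on incident HIV in people with no earlier evidence of infection, so known positives are not its target. The move from 1.4% to 5% has no support in the article. All of this stands and limits the size of the point. It does not repair the definition, and with testing expected to double in a deliberately different mix, a constant share would be an assumption that the article does not state.

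A second reply is that diagnoses per test completed is a coherent yield measure, and that the article itself expects the rate to rise through targeting. It is true that the rate measures case-finding rather than incidence. But a yield per test needs either all positives over all tests, as in the article's STI positivity, or new positives over tests that could have been new.

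A reader might also infer that the record used to recognise prior HIV changes at go-live, making known cases more visible afterwards. The article does not say so. The match at jail entry is described as serving the risk score: "Our automated algorithm will match the jail EHR to the Parkland EHR and generate an individual HIV risk score". The model ready for deployment uses jail data, and "Future exercises will include integration with health system EHR data from Parkland Hospital". The matched data reach back to 2010, and Ethical Considerations reports the matching in the past tense, so one look-back could serve both periods. Differential recognition remains a possible risk, because the record source for the chart review is not named, but it is not a documented feature. A condensed article may leave that source to the fuller protocol.

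**Conclusion.** The point holds as a mismatch in the stated definition. Numerator and denominator cover different populations, and the before/after ratio carries a factor (1 − k1)/(1 − k0) that has nothing to do with yield among people at risk. Over the assumed shares shown, a planned 1.50 becomes anything from about 1.45 to 1.58. A shift from 1% to 3% alone uses most of the margin above 80% power (84.6% to 80.6%, months independent). Equal shares give no bias.

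The size rests wholly on assumed shares, and the direction is not known. The documents do not support a claim that the comparison is seriously compromised or that case classification differs between the periods. The point is modest, and worth correcting because the correction costs little.

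**What to change.** 1. Define the denominator as tests completed in persons without a prior HIV diagnosis at the time of the test, to match the numerator.
2. Determine prior-diagnosis status with the same record source and look-back rule in all 48 months. The existing jail–Parkland match, with data from 2010, can be applied to both periods. This also removes the possible risk of unequal recognition of prior HIV.
3. Report the known-HIV share of tests by month, so that readers can see whether it moved.

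The cost is a change of wording in the outcome definition and one retrospective run of a matching algorithm that already exists. Previously known diagnoses are already to be tracked, so the tests to remove should be largely identifiable. No clinical procedure changes. Masking those who review charts to the period is optional and not part of this fix.
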